# A protocol for a randomized comparison of extended-release versus sublingual buprenorphine among pre-trial detainees in jail

**DOI:** 10.1186/s13722-025-00611-9

**Published:** 2025-10-27

**Keywords:** Extended-release buprenorphine, Jail, Corrections, Massachusetts, Medication for opioid use disorder, Pre-trial

## Abstract

**Context/background:**

The high prevalence of opioid use among jailed adults offers an unmatched opportunity to identify and treat those with opioid use disorder (OUD), a population that is at a substantial risk for post-release overdose. From a public health perspective, jails are critical touchpoints, as these facilities typically admit more than 7 million adults per year. One clinical consideration is whether pre-trial detainees with OUD would benefit from early induction onto extended-release buprenorphine (XRB).

**Methods/study design:**

In this 3-year randomized controlled trial, we will identify and recruit 200 incarcerated adults with OUD who are receiving sublingual buprenorphine (SLB) or tolerate a SLB test dose and randomize them to receive extended release buprenorphine (XRB) (*n* = 100) or to remain on SLB (*n* = 100) while in custody. Study participation will continue through their pre-trial time in jail (up to 6 months) or until they are sentenced or released. Community treatment will then be tracked for 90 days following release. In addition to collecting data on XRB uptake in jail, we will assess (1) the percentage of XRB and SLB study participants leaving jail with a clinically active dose of buprenorphine in their system, (2) 90- day post-release MOUD continuation, (3) levels of buprenorphine diversion while in custody, and (4) recidivism and death (90 days). “Clinically active” is defined as receiving XRB within the past 28 days or SLB in the past 24 h.

**Discussion:**

Findings from this study will demonstrate the feasibility and outcomes of inducting pre-trial adults with OUD onto XRB, as well as offer practical clinical and policy guidelines for best practices for treating this high risk and understudied population.

## Introduction

### Context/background

Due to the high prevalence of opioid use and elevated risk of overdose among justice involved adults, jails offer an unmatched opportunity to identify and offer treatment to those with opioid use disorder (OUD). From a public health perspective, jails are critical intervention touchpoints, as these facilities typically admit more than 7 million adults per year in the US, holding individuals for an average of 32 days prior to release [1]. In Massachusetts, individuals released from incarceration have a 120 times higher rate of opioid-related overdose deaths compared to the remainder of the adult population [2]. Some jails have responded to the opioid crisis by expanding access to medication for opioid use disorder (MOUD) [3]. However, the optimal strategies for providing MOUD in jails—such as the most appropriate type and timing of treatment—are not well established.

One clinical consideration is whether XRB should be offered to pre-trial detainees with OUD. Relative to its more commonly used counterpart—daily SLB—XRB offers several potential advantages in jail, including: easier logistics of administration, reduced risk of diversion, reduced experiences of patient stigma due to the less regular dosing schedule, and an increased bridge of protection between the time of discharge and admission to community-based MOUD [4]. In prior analyses in Massachusetts jails, it was found that typical SLB retention rates upon release to the community were 80.6% for those prescribed SLB and 86.7% for those prescribed methadone within 30-days of release [5] (Personal communication), and a number of barriers to community connections and ongoing MOUD treatment continuity could lead to breaks in continued buprenorphine and methadone treatment [6, 7] (Stopka et al., 2024; Matsumoto et al., 2023). Because the release date for pre-trial detainees is variable and uncertain, early induction could ensure that persons released precipitously (e.g., from court without notice) will have a clinically active dose of buprenorphine in their system to protect them against post-release overdose. Early induction onto XRB is also more expensive than SLB.

The relative benefits of XRB versus SLB for patients in jail have yet to be established empirically, but a jail-based pilot study provides some reason for optimism [8]. A randomized comparison of 52 sentenced participants (half receiving XRB; half SLB) found that patients receiving XRB had fewer jail medical visits compared to those with daily SLB medication administration, higher enrollment in post-release community treatment (69% vs. 35%), and higher rates of opioid-negative urine tests following release (55% vs. 38%). These findings are promising and merit replication with a larger sample. It would be further beneficial to replicate that study with pre-trial detainees rather than sentenced residents, as the former account for more than 70% of the U.S. jail population [1], and are at greater risk for discontinued treatment and overdose given limited time for pre-release planning. In this study, 200 pre-trial detainees receiving SLB in a Massachusetts jail will be randomized to SLB treatment or transition to XRB treatment.

### Differences between SLB and XRB

SLB is a partial opioid agonist that is administered orally on a daily basis to those with OUD. The medication typically comes in a pill, tablet, or film, which is dissolved under the tongue. SLB dosages start at 2 mg and can be increased in 2 mg increments as deemed appropriate by medical and nursing staff. XRB is an extended-release version of buprenorphine and is indicated for the treatment of moderate to severe OUD in patients. XRB is a monthly injectable medication which is delivered subcutaneously to the abdomen, thigh, buttock, or back of the upper arm. A depot is formed at the injection site, which slowly releases the medication into the body. The XRB dose starts at 300 mg injection for the first two months, usually followed by a maintenance dose of 100 mg monthly thereafter depending on the clinical insights of the prescribing provider.

## Methods

### Overview of study design

This three-year research project will recruit 200 participants at the Middlesex Jail and House of Correction (MJHOC). The two-group randomized trial will assess the potential benefits of offering XRB to pre-trial detainees. Participating pre-trial detainees receiving SLB will be randomized 1:1 to transition to XRB as soon as possible or remain on SLB during their jail term (or up to six months). Per usual treatment for MOUD recipients at the jail, all efforts will be made to refer participants to receive MOUD treatment in the community upon release. We will compare (1) the percentages of XRB and SLB participants leaving jail with a clinically active dose of buprenorphine in their system, (2) infractions for diverting buprenorphine while incarcerated, (3) community MOUD intake and retention, and (4) 90-day recidivism or death. The final three months of the study will be devoted to data cleaning and analysis, study close out, preparation of manuscripts, and dissemination.

### Study population

Potential study participants will be pre-screened and then approached by research staff. If the participant is interested, they will undergo final screening and will be invited to complete the informed consent process. The screening criteria are described below.

#### Inclusion criteria

Incarcerated pre-trial detainees are able to provide written informed consent in English;They are currently receiving SLB, which will be verified via the jail’s electronic medical system and medical staff, or have confirmed current OUD and tolerate a SLB test dose;They are willing to accept random assignment to the experimental or control condition (i.e., transitioning to XRB while incarcerated or continuing on SLB).

#### Exclusion criteria

Sentenced detainees;Based on charges, the anticipated jail stay is less than 4 days (e.g. larceny, license suspended, shoplifting, vandalize property). The estimated typical jail stay times will be made based on charges verified using the jail management system.

#### Participant recruitment

Following pre-screening, trained research staff will approach potential participants and inform them about study participation. Individuals who meet eligibility criteria and state clear interest in study participation will be invited to voluntarily complete the informed consent process. To ensure privacy, all pre-screening, screening, consenting, and interviews will take place in a private space, such as a medical exam room or space designated for attorney visits, or a private space on the unit. To further enhance confidentiality, the research staff will receive clearance at the jails as contractors so they will not need to disclose information to correctional staff when accessing prospective or enrolled participants’ information via the electronic medical records system or the jail offender management system.

Enrollment must be voluntary, and all participants can expect to benefit, in keeping with Office for Human Research Protections (OHRP) federal prisoner research standards. Enrollment status and study data or results will not be shared with judicial or correctional authorities, unless specifically authorized by the participant (Fig. 1).

**Fig. 1 Fig1:**
[figure not shown]
Study flow

### Treatment-as-usual procedures for jail inmates

Treatment-as-usual at MJHOC is provided through the Medication Assisted Treatment and Directed Opioid Recovery (MATADOR) program. MATADOR is a voluntary treatment option for individuals who meet eligibility criteria. This program offers all three forms of Food and Drug Administration (FDA) approved medications to treat OUD: methadone, buprenorphine, and naltrexone in combination with counseling, behavioral health therapies, post-release navigation supports, and helps connect patients to treatment providers in the community post-release. Through this program, participants receive support services from MJHOC staff to work towards their recovery and develop a long-term individualized treatment plan. Additional support from MJHOC Patient Navigators (PNs) and Recovery Coaches is available to help with transitioning back to the community post-release. This is the standard of care for all MOUD patients at the jail.

Recruitment targets were based on numbers provided by the MATADOR program indicating that between January 2024 and March 2025, MSO enrolled on average 16 pre-trial patients per month who were receiving daily buprenorphine, with a range of 8–26 enrollments and a median of 16. In addition, we plan to expand enrollment to pre-trial incarcerated adults on SLB who are not recent admissions but are within 90 days of anticipated release.

### Study sites

The site for participant recruitment, data collection, and treatment will be the MJHOC. Middlesex is the most populous county in Massachusetts and New England [9]. The facility includes a House of Correction, which holds people who are sentenced, and a jail, which holds people awaiting trial. As of June of 2025, 526 pre-trial detainees were being held at MJHOC [[name], 2024, 2 Questions, personal communication]. This study will only include unsentenced, pre-trial detainees (Table 1).

**Table 1 Tab1:** Data sources and measures

Measures	Data source	Screening	Pre-release	Post-release
Screening (adult, SLB, unsentenced, 4 days-6 months anticipated jail stay, willing to be randomized)	Electronic medical record (CorEMR), Offender Management System (OMS), self-report	X		
Baseline	Self-report		X	
* Demographics*				
* OUD history*				
* MOUD history*				
Dosing schedule (SLB and XRB)	CorEMR		X	
Liver function test (LFT)	CorEMR		X	
Urine drug screening	CorEMR		X	
Medication diversion incidents	OMS and Inner Perimeter Security (IPS) unit		X	
Number of days Buprenorphine protection post-release (7 days)	CorEMR, OMS			X
Enrollment in community based MOUD (90 days)	Community clinics			X
* # of appointments*				
* Medication type*				
* Dose amount*				
Recidivism (90 days)	Criminal Justice Information Services (CJIS)			X
* # of arraignments*				
* Types of charges/offenses*				
* # of incarcerations*				
* # of convictions*				
Death (90 days)	Various sources (Massachusetts Office of vital statistics, National death index, Google)			X

### Outcome measures

The study is assessing the impact of offering XRB to pre-trial incarcerated adults, as compared to those maintained on SLB (treatment as usual). Descriptive statistics will provide an overall assessment of the implementation of the protocol.

#### Primary outcome measure

The primary outcome measure is the percentage of participants who leave with a clinically active dose of buprenorphine in their system.

#### Secondary and tertiary outcome measures

The secondary outcome measure is MOUD continuation in the community. This outcome will be based on community clinic records indicating admission and retention at 90-days following release, measured as the number of SLB doses or XRB injections received in the community. Tertiary outcome measures involve a range of incidents including death, diversion, disciplinary actions, as well as recidivism outcomes at 90 days post release. Recidivism will be defined as arraignments, types of charges/offenses, incarcerations, and convictions. Data will be acquired through the jail from Criminal Justice Information Services (CJIS) records.

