##### Dosing timelines and release

In both SLB and XRB conditions, patients will be encouraged to continue their treatment outside of the facility. Both forms of treatment that are offered in the study are available to participants in the community. Designated MATADOR staff at the MJHOC create appointments for patients to continue receiving their medication in the community. These appointments are set up prior to release, however it is the patients’ responsibility to follow through with these appointments and continue their treatment. Patients are also given a bridge script for their medication prior to discharge in attempt to avoid lapses in treatment.

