###### XRB maintenance

Participants will receive XRB monthly from the time of induction to the day of release, sentencing, or transfer. Study clinicians will generally adhere to FDA-labeling on XRB dosing, which recommends two months of 300 mg doses followed by maintenance doses of 100 mg monthly for the remaining four months. The maintenance dose may be increased to 300 mg monthly for patients who tolerate the 100 mg dose, but do not demonstrate a satisfactory clinical response, as evidenced by self-reported illicit opioid use or urine drug screens positive for illicit opioid use. Indivior data indicates that 300 mg continuous dosing may be more effective for people experiencing fentanyl-involved OUD. XRB can be administered subcutaneously in the abdomen, thigh, buttock, or back of the upper arm at each 28-day visit with a minimum of 26 days between doses. In the event of a missed visit, the dose can be delivered within 28 days (up to 8 weeks since the prior dose). Longer missed dose windows will require another brief SLB lead-in prior to the next injection.

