## Results/hypotheses

### Planned analyses

The approach for testing the primary hypothesis— that administering XRB to pretrial detainees will result in a significantly higher proportion of participants being released with a clinically active dose of buprenorphine in their system than will SLB (TAU) participants— will use generalized linear models with a log-binomial link to generate risk ratios for the study groups. Outcome measures for the secondary outcomes include rates of enrollment in community MOUD following release from jail. We will also assess group differences in the infractions for diversion and recidivism. Differences across treatment arms (e.g., disciplinary infractions) will be assessed using generalized linear models depending on the nature of the outcome. In the case where there are repeated measurements for each individual (e.g., buprenorphine treatment continuity at X, Y, Z months), mixed effect models will be used with participant-level random effects.

This study is powered to detect a medium effect size corresponding to a risk ratio of 1.34 (OR = 2.4), assuming 75% are released from jail with a clinically active dose of buprenorphine in their system in the XRB condition, a two-tailed test, and a power of 0.80. Because the desired outcome is expected to be rare under the SLB condition, we also consider the precision of the primary outcome prevalence estimate under the XBR condition given the total sample size (*n* = 200). With *n* = 100 participants in the XBR condition and 0.75 expected for the prevalence of the primary outcome, the 95% confidence interval width is 0.168 (i.e., 0.657–0.825).

Retention-in-study-medication-treatment will be tracked using administrative data. We will make every attempt to confirm suspected deaths, cause-of-death, and relevant collateral data through participant contacts, public information, and public death data.

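### The 90-day retention measure counts SLB doses or XRB injections, so equal treatment scores about 90 on one formulation and 3 or 4 on the other

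*Protocol article*

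**What the plan says.** Under Secondary and tertiary outcome measures, the secondary outcome is MOUD continuation in the community. It is taken from community clinic records and has two parts: admission, and "retention at 90-days following release, measured as the number of SLB doses or XRB injections received in the community". The Abstract sets the window: "Community treatment will then be tracked for 90 days following release".

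The two products run on different schedules. Differences between SLB and XRB states that "SLB is a partial opioid agonist that is administered orally on a daily basis to those with OUD" and that "XRB is a monthly injectable medication which is delivered subcutaneously". XRB maintenance gives the interval: injections "at each 28-day visit with a minimum of 26 days between doses". The Abstract's definition of a clinically active dose reflects the same difference: it "is defined as receiving XRB within the past 28 days or SLB in the past" 24 hours.

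Planned analyses describes the community outcome in other terms. It says "Outcome measures for the secondary outcomes include rates of enrollment in community MOUD following release from jail". In its intention-to-treat paragraph it codes post-release MOUD participation as No for people who were not released, which implies a yes/no variable. Table 1 lists number of appointments, medication type and dose amount for community MOUD over 90 days. Its only measure in days of protection covers 7 days after release and comes from jail records.

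**The concern.** One counted unit stands for one day of treatment on SLB and for 28 days on XRB. Formulation is what the trial randomizes, and Dosing timelines and release says both arms are encouraged to carry on with their treatment after release. The counting artefact will therefore tend to follow the arm. A comparison of mean counts would mix any real difference in retention with a much larger difference in dosing frequency, and the artefact works against XRB.

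The count is also narrower than the outcome it is meant to measure. The outcome is named for MOUD in general, and the treatment-as-usual section says the jail program offers methadone, buprenorphine and naltrexone. A participant who moves to methadone and stays on it would add nothing to the count while remaining in treatment.

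**Working it through.** **The plan's own figures.** The article gives no power or expected value for this outcome, so there is no stated figure to reproduce for it. The sample size rests on the primary outcome and does reproduce. A risk ratio of 1.34 with 75% on XRB implies 0.75/1.34 = 0.560 on SLB. With 100 per arm and a two-sided 5% level (assumed; the article gives no level), power is 0.813 against the stated 0.80. Nothing below alters that.

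**Score for complete treatment over 90 days**, taking release as day 0 and the window as days 0 to 89:

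- SLB, daily: 90 doses.
- XRB, every 28 days: 90/28 = 3.2. If the first community injection falls on days 0 to 5, four fit (day 5 gives 5, 33, 61, 89). If it falls on days 6 to 28, three fit (day 28 gives 28, 56, 84).
- XRB at the 26-day minimum: 3 or 4. At a 30-day month: 3.
- Ratio: 90/4 = 22.5 to 90/3 = 30.

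**Break-even.** An SLB participant who stops after 3 or 4 days equals an XRB participant treated throughout. One who stops after a week (7 doses) scores higher.

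**Switching after release.** The article gives no switching rate, so these are assumptions. Everyone is fully treated and a full XRB course counts as 3.

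| XRB arm moving to SLB | SLB arm moving to XRB | Mean, XRB arm | Mean, SLB arm | Ratio |
|---|---|---|---|---|
| 0% | 0% | 3 | 90 | 30 |
| 25% | 0% | 0.75×3 + 0.25×90 = 24.75 | 90 | 3.6 |
| 50% | 0% | 0.50×3 + 0.50×90 = 46.5 | 90 | 1.9 |
| 50% | 10% | 46.5 | 0.90×90 + 0.10×3 = 81.3 | 1.7 |

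True retention is identical in every row, so each ratio above 1 is spurious. It reaches 1 only when both arms have the same formulation mix.

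**Direction.** The Introduction cites a pilot with post-release enrollment of 69% on XRB and 35% on SLB. Purely as an illustration, treat those as the shares fully retained. Mean counts are then 0.69×3 = 2.1 and 0.35×90 = 31.5. An advantage for XRB would appear as a roughly 15-fold deficit.

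**The case against.** The strongest reply is that the article nowhere says raw counts will be pooled and compared between arms. Planned analyses speaks of enrollment rates, leaves the model to the type of outcome, and treats participation as yes/no. Admission is itself part of the secondary outcome and is a yes/no event. A reader might infer that the whole secondary outcome is distorted, or that the main post-release question must be answered wrongly. The documents do not support that: admission, enrollment and participation do not depend on formulation. What remains is that retention has its own stated measure, that enrollment does not measure retention, and that nothing says the yes/no versions replace the count.

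A second reply is that the unit follows the product received in the community, not the arm. This is right. Random assignment says allocation to XRB does not guarantee induction, and both products are available after release. The 22- to 30-fold gap is therefore the no-switching case, not an expected value.

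A third reply is that scoring detail belongs in the full protocol or the analysis plan. That would answer an omission. Here the article states a measure, and an analysis plan that followed it would inherit the problem.

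Two further criticisms are tempting and should not be pressed. Because "Patients are also given a bridge script for their medication prior to discharge", a reader might infer that clinic records miss SLB doses taken at home, but the article does not describe what those records contain. A reader might also call it an error to ignore the last in-jail injection. The outcome concerns treatment in the community, so leaving that injection out is a defensible choice. Counting it would credit someone injected on the day of release with 28 of 90 days (31%) without a single community visit, which overlaps with the primary outcome and favors XRB by construction.

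**Conclusion.** The point holds for the retention part of the secondary outcome. As stated, the count puts full treatment at about 90 on SLB and 3 or 4 on XRB. Compared between arms, it would show a large spurious deficit for XRB: 22- to 30-fold if participants stay on their assigned product, and about 3.6- or 1.9-fold under assumed switching of 25% or 50% of the XRB arm. It also omits methadone and naltrexone. These sizes assume complete treatment in both arms, and the switching rates are illustrative.

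The primary outcome, the sample size, and the admission, enrollment and yes/no participation measures are unaffected. The harm arises only if the count is used to compare arms, which the article neither states nor rules out.

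**What to change.** For the between-arm comparison of retention, replace the count with one measure that does not depend on formulation: in treatment with any MOUD at day 90, yes or no. Support it with days covered out of 90 from community treatment, counting 28 days per community XRB injection, one day per SLB day supplied, and days on other MOUD. Use the same definition in the Abstract, in Secondary and tertiary outcome measures, and in both the model and intention-to-treat paragraphs of Planned analyses. Report dose and injection counts only as description within each formulation.

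Carry-over from the last in-jail injection, if counted at all, belongs in a sensitivity analysis. Leaving it out of the supporting measure has a price: an XRB participant whose first community injection falls on day 28 can reach at most 90 − 28 = 62 community-covered days. This is why the day-90 status should lead and the days-covered result should be read with and without carry-over.

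The cost is a change of wording and some extra derivation. Table 1 already lists appointments, medication type and dose amount. If the clinic records do not also give injection dates and SLB days supplied, those would need to be requested. The change should be made before outcome data are examined by arm.

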##### XRB injection procedures

###### XRB induction

Patients randomized to the XRB condition will first receive a 4 mg dose of sublingual buprenorphine followed by the XRB injection an hour later, if there is no precipitated withdrawal, based on package insert recommendations. XRB will be delivered as a pre-filled 2 cc subcutaneous monthly injection, using a 300 mg starting dose in most cases. Study staff may elect to use the 100 mg dose for initial injection, if over-sedation is deemed to be a higher-than-average risk (for instance, if the participant experienced over-sedation during the SLB up-dosing). XRB consists of a depot injectable formulation in polymeric solution to the abdomen and releases buprenorphine over 28-days (4-weeks) by diffusion as the polymer biodegrades.

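### The secondary outcome counts SLB doses or XRB injections without a common unit, so as worded it tracks the formulation taken rather than treatment continuation

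*Protocol article*

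**What the plan says.** Under Secondary and tertiary outcome measures, the protocol article states: "The secondary outcome measure is MOUD continuation in the community". The source is "community clinic records indicating admission and retention at 90-days following release", and the outcome is "measured as the number of SLB doses or XRB injections received in the community". No conversion between a dose and an injection is given.

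The two products differ in dosing frequency. Differences between SLB and XRB says "SLB is a partial opioid agonist that is administered orally on a daily basis" and "XRB is a monthly injectable medication". XRB induction and XRB maintenance give the injection interval as 28 days.

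Other sections describe the outcome differently:

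- Overview of study design refers to community MOUD intake and retention.
- Table 1 lists 90-day enrollment in community MOUD, with the number "of appointments", medication type and dose amount.
- Planned analyses names rates of community enrollment. It foresees mixed models for treatment continuity at several time points. In the ITT analysis it codes post-release participation as No for people who are not released.
- Dosing timelines and release says that both formulations are available in the community.

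**The concern.** The unit of the count depends on the product: one SLB dose stands for a day of treatment and one XRB injection for 28 days. The product is also what the trial randomises. Two participants with identical continuation therefore get very different scores if they take different formulations.

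If an analyst followed the outcome section literally and compared these counts between arms, the result would mostly show who was on which product. A true advantage of XRB in retention could appear as a large disadvantage. An XRB-arm participant who moved to SLB after release would raise that arm's mean with no change in continuation. Planned analyses chooses the generalized linear model according to the nature of the outcome, so an outcome defined as a count invites a count model.

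**Working it through.** The article gives no sample size, power or expected value for the secondary outcome, so there is no figure of the plan's own to reproduce.

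**Inputs from the article.** Follow-up is 90 days after release. SLB is daily. XRB is every 28 days. The cited jail pilot found post-release treatment enrollment of 69% (XRB) and 35% (SLB) (Introduction).

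**Assumptions made here, for illustration only.** The last in-jail injection falls uniformly over the 28 days before release. Pilot enrollees are retained for all 90 days and everyone else for none. Participants stay on their assigned formulation unless stated.

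**1. Score at full retention.**
- SLB: 90 × 1 = 90 doses.
- XRB: the first community injection falls due V days after release, with V uniform on 0 to 28, and then every 28 days. A fourth injection fits if V + 84 ≤ 90, that is V ≤ 6, with probability 6/28 = 21%. Otherwise there are three (79%). Mean = 3 + 6/28 = 3.21.
- Ratio: 90/3.21 = 28. With whole injections it is 90/3 = 30 or 90/4 = 22.5.

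**2. What a raw-count comparison would show at the pilot rates.**
- XRB mean: 0.69 × 3.21 = 2.2 (2.1 with three injections, 2.8 with four).
- SLB mean: 0.35 × 90 = 31.5.
- SLB to XRB ratio: 31.5/2.2 ≈ 14 (range 11 to 15), against the direction of retention.

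**3. The same behaviour on a days-covered scale.**
- All treatment days counted: XRB 0.69 × 90 = 62.1; SLB 0.35 × 90 = 31.5.
- Community-provided days only: a fully retained XRB participant is covered for 90 − V days, mean 90 − 14 = 76, so the XRB mean is 0.69 × 76 = 52.4 against 31.5 if SLB is supplied in the community from day 1.
- Both versions favour XRB, in line with the assumed retention.

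**4. Sensitivity to switching.**
- At full retention, if 10% of the XRB arm moved to daily SLB, its mean count would be 0.1 × 90 + 0.9 × 3.21 = 11.9 instead of 3.2, with no change in continuation.
- At the pilot rates, the raw-count reversal disappears when a share s of retained XRB-arm participants take SLB, where 0.69 × [(1 − s) × 3.21 + s × 90] = 31.5. This gives s = (45.65 − 3.21)/(90 − 3.21) = 0.49.

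**5. The forms in Planned analyses.** An enrollment rate, continuity at a time point and a Yes/No code each score a retained participant the same on either product. None has this unit problem.

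**The case against.** The strongest reply is that the article never says doses and injections are added together or compared as one raw number. The wording is an alternative (or), and the same sentence bases the outcome on admission and 90-day retention. Counting each product in its own unit can be a step towards establishing retention. Planned analyses names rates, continuity and a Yes/No code, and no model of the raw dose count is specified. How clinic records become a retention variable is often left to an SAP, which is not shown here.

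Much of this stands. A reader might infer that the plan sums the two units, that the arm comparison will reverse, or that the trial cannot answer its continuation question. The article supports none of these. The ratio of 28 attaches to the formulation taken in the community, not to the randomised arm: both products are available to everyone after release, and Random assignment says that allocation to XRB does not guarantee induction. The 14-fold figure also needs no switching and all-or-nothing retention, at enrollment rates from a 52-person pilot in sentenced participants.

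The reply does not rescue the definition. If each product is counted separately, participants on different products still share no scale. Planned analyses says only that secondary outcome measures include enrollment rates; enrollment is not 90-day retention, and the No code is described for people never released. This is a stated rule rather than a missing detail. An SAP that follows it inherits the problem, and one that departs from it contradicts the published definition.

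One might also object that a community-only count ignores days still covered by the last in-jail injection. The outcome is continuation in the community, and Table 1 has a separate item for days of buprenorphine protection after release (7 days). Whether to credit those days is a choice of estimand, not an error. No between-arm comparison of appointment counts is specified either.

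**Conclusion.** The point holds as a defect in the stated definition. The only measurement rule in the outcome section uses units that cannot be compared across formulations: about 90 against 3 or 4 for the same 90 days of full retention. That ratio rests only on the article's dosing intervals and its follow-up period.

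The consequence for the arm comparison is conditional. If the count were compared between arms as worded, it would reflect formulation and switching, and it could favour SLB despite higher XRB retention. The size of any reversal depends on the assumptions listed in the working, and with about 49% or more of retained XRB-arm participants switching it would not occur at the pilot rates. Analyses of enrollment, continuity or a Yes/No outcome would not reverse for this reason. What is certain is that the outcome section and Planned analyses describe different forms of the same outcome, and that one of them is unsuitable for the comparison.

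**What to change.** In Secondary and tertiary outcome measures, replace the count with one of these:

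- in treatment at day 90 after release (yes/no); or
- the proportion of the 90 days covered by community-provided treatment. Each SLB day supplied counts as 1 day and each XRB injection as 28 days (the article's own interval), with overlapping days counted once and the total capped at 90.

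Then align Planned analyses, including the ITT coding, to the chosen form. Report raw dose, injection and appointment counts descriptively by formulation only. Put any credit for unexpired in-jail injection days or bridge-script supply in a sensitivity analysis, under the same rule in both arms. For the days-covered version this matters, because the community-only rule leaves out on average 14 of the 90 days for a fully retained XRB participant under the uniform assumption above.

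The cost is small: a revised sentence, a short derivation rule and matching edits to Planned analyses. Table 1 already collects medication type and dose amount, but it does not list SLB days supplied, so the days-covered version needs confirmation that clinic records give them. Final outcomes are expected by spring 2027, so the definition can be settled before analysis.
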